## Abstract

**Background:**

Community mobilization (CM) interventions show promise in changing gender norms and preventing HIV, but few have been based on a defined mobilization model or rigorously evaluated. The purpose of this paper is to describe the intervention design and implementation and present baseline findings of a Cluster Randomized Controlled Trial (RCT) of a two-year, theory-based CM intervention that aimed to change gender norms and reduce HIV risk in rural Mpumalanga province, South Africa.

**Methods:**

Community Mobilizers and volunteer Community Action Teams (CATs) implemented two-day workshops, a range of outreach activities, and leadership engagement meetings. All activities were mapped onto six theorized mobilization domains. The intervention is being evaluated by a randomized design in 22 communities (11 receive intervention). Cross-sectional, population-based surveys were conducted with approximately 1,200 adults ages 18–35 years at baseline and endline about two years later.

**Conclusions:**

This is among the first community RCTs to evaluate a gender transformative intervention to change norms and HIV risk using a theory-based, defined mobilization model, which should increase the potential for impact on desired outcomes and be useful for future scale-up if proven effective.

**Trial registration:**

ClinicalTrials.gov NCT02129530

## Background

Social environments and social norms that are not supportive of safer sexual behaviors place young men and women at extremely high risk of HIV/STI acquisition [1–3]. In South Africa social constructions of masculinity and femininity have been demonstrated to increase risk of HIV infection and other negative health outcomes, such as intimate partner violence and alcohol abuse [4–9]. Norms of masculinity in this setting place value on multiple sexual partnerships and condone physical and sexual violence as a means of establishing power in relationships with female partners [6, 7, 9]. Further, norms of masculinity often deter men from accessing health services, resulting in poor uptake of preventive care services, including HIV testing and care [10–15].

Gender transformative interventions, which seek to reconfigure gender roles in the direction of more gender equitable relationships, [16] have demonstrated some success in changing norms and reducing risk behaviors [17–19]. While numerous gender transformative interventions have been undertaken worldwide, only a small number have been rigorously evaluated using an experimental design [17, 18]. Evaluations suggest that combining group education with Community Mobilization (CM) strategies, or those that engage communities to dialogue and take action around shared concerns, [20] may be more effective in changing norms and risk behaviors than group education alone [17, 18, 21]. CM strategies have also shown promise in creating more supportive social environments and social norms to reduce HIV risk and promote safer sexual behaviors [3, 17, 22–30]. To date, however, very few gender transformative programs with a CM approach have been designed around a defined theoretical model of community mobilization.

The aim of this paper is to describe the intervention and study design of a Cluster Randomized Controlled Trial (RCT) of a novel, theory-based CM intervention to change gender norms that place communities at risk of HIV acquisition. The two-year trial was implemented from May 2012 to June 2014 in the rural Bushbuckridge sub-district in Mpumalanga province of South Africa. This is among the first community RCTs to evaluate a gender transformative intervention to change negative gender norms and HIV risk, and to our knowledge, is the first to do so using a defined mobilization model [20, 31].

## Methods

### Intervention design

The primary objectives of the CM intervention were to increase awareness about the relationship between gender inequities and HIV and encourage the community and especially men to take action to address negative gender norms and HIV risk. The CM intervention was designed in partnership with the South African non-governmental organization Sonke Gender Justice, based on their One Man Can (OMC) Campaign. OMC was originally designed in 2006 as a program to promote healthy, equitable relationships and support men and boys to take action to end domestic and sexual violence. Trained community mobilizers carry out intensive two-day workshops on themes related to gender and health; a range of community outreach activities; and assist in establishing and training volunteer cadres called Community Action Teams (CATs) in each community (www.genderjustice.org.za). These intervention elements then become a catalyst to mobilize community members to take action in their own homes and neighborhoods.

The CM intervention included similar workshop structure and types of community activities, implementation by mobilizers and emphasis on CAT engagement, however for this study, thematic content and activities were extended more specifically to address HIV risk and a more a direct focus on engaging community leadership was added. Aspects of the OMC campaign that included use of the mass media for advocacy work were not included in the CM intervention, in efforts to avoid intervention contamination in comparison communities. All intervention components were carefully mapped onto a theoretical framework for CM developed through extensive formative work by the investigative team, comprising six targeted domains. These CM domains include: 1) development of a shared concern (around HIV and gender norms); 2) building critical consciousness; 3) establishing and leveraging organizations and groups, including links to networks; 4) engaging leadership (individual and/or institutional); 5) engaging communities in collective activities/actions; and 6) building social cohesion [20]. The theoretical framework is included in Fig. 1.

**Fig. 1 Fig1:**
[figure not shown]
Conceptual framework of the intervention, community mobilization domains, and outcomes

The Intervention was implemented by a team of two supervisors, 15 community mobilizers, and at least one CAT in each community, which on average included about eight members. Community mobilizers were selected from among men and women ages 18–35 in the communities receiving the CM intervention. Mobilizers underwent an intensive initial month-long training as well as ongoing training led by the CM intervention manager (DR) who had over 10 years of experience conducting gender awareness and mobilization-related community work. Mobilizers in turn were responsible for conducting initial and refresher trainings for CAT members, with guidance from the CM intervention managers.

Intervention workshops included both men and women and addressed seven content areas, including (1) gender, power, and health, (2) gender and violence, (3) alcohol, (4) gender, HIV and AIDS, (5) healthy relationships, (6) human rights, and (7) taking action for change. Mobilizers and CATs also created opportunities for community dialogue about these themes outside of workshops through community activities focusing on developing a shared concern and critical consciousness around HIV and gender. Examples of community activities included door-to-door home visits, street soccer and soccer tournaments, mural design and discussions, “digital story” (short testimonial film) and other film screenings with a thematic discussion to follow, health talks, and ambush theater (in which actors act out a scene in a public place, then reveal themselves and engage the crowd in conversation over the scene they witnessed). The team also engaged formal leadership in each community to discuss the intervention themes and seek support and collaboration for activities applicable to the local context of each community. A matrix showing how each of these intervention components maps onto the theorized CM domains is included in Table 1.

**Table 1 Tab1:** Intervention activities mapped onto Community Mobilization domains

	Shared concerns	Community conscious-ness	Orgs/ Networks	Leadership	Collective Action	Social cohesion
Establishing Community Action Teams (CATs)			X	X		X
2-day small group workshops	X	X				X
Engaging leadership			X	X		
Community activities						
• Mini (2–3 hour) small group workshops	X	X		X (leaders workshop)		X
• Shebeen (tavern) workshops	X	X	X			
• Ambush theater	X	X				
• Door to door outreach	X	X				
• Digital stories screenings	X	X				
• Community murals					X	X
• Street soccer	X	X				
• Soccer tournaments			X	X	X	X
• Debates	X	X				
• Community events/ forums/ cultural event	X	X	X		X	X
• Film screenings with discussion	X	X				
• PhotoVoice workshops	X	X		X	X	X

All CM intervention activities were manualized and implemented with systematic targets for implementation in terms of intervention dose delivered and intervention reach within the target population. The target audience for the intervention was men and women ages 18–35 (the resident target population was approximately 25,000), although all adult community members were welcomed in workshops and community activities and events.

### Monitoring intervention implementation

Monitoring data was used to track intervention dose delivered, reach and activity mix. Data was captured using paper-based monitoring forms completed by the community mobilizers and CATS and entered into a database weekly. Targets for dose delivered for each community differed slightly by community size (larger vs. smaller communities) and included 1–2 workshops per month, 4–8 activities per week (16–32 activities per month), and 2 leadership engagement meetings per month (reduced to 1 in year 2). Targets were also set to reach 20 % of the male population age 18–35 living in the intervention communities (overall and by community) with at least one workshop in the first year and 40 % by the end of the second year. Reaching 40 % of the population by the end of the intervention was chosen as a potentially appropriate target as it is nearly three times the 15 % commonly thought of as a ‘critical mass’ of a population’s opinion leaders for successful diffusion of health behavior change messages [32]. Activity mix was monitored to ensure all content themes and mobilization domains were addressed.

### Study setting

The study setting for this community RCT includes 22 villages in the Agincourt Health and Socio-Demographic Surveillance Site (Agincourt HDSS) in the rural Bushbuckridge sub-district in Mpumalanga province of South Africa [33]. The study site is located about 500 km northeast of Johannesburg, near South Africa’s border with Mozambique. HIV prevalence in Mpumalanga is estimated to be 21.8 % among adults ages 15-49 [34] and prevalence among 35–39 year olds in the study area was over 45 % in 2010–2011 [35].

### Study design

This study employed a community randomized design to evaluate the impact of the CM intervention in 22 communities (11 intervention) in the study catchment area. To measure the impact of the intervention and monitor changes in study outcomes and the CM domains in each community, two cross-sectional, population-based surveys were implemented among approximately 1,200 randomly sampled adults, ages 18–35 years. The cross-sectional surveys were conducted at baseline in March-June 2012 (prior to intervention implementation) and again in July-September 2014, following approximately two years of intervention implementation. Serial cross-sectional samples were chosen instead of a panel design due to high levels of in- and out- migration in the study population as well as the advantages for measuring community-level indicators and community change in each village.

This study was approved by the Institutional Review Boards at the University of North Carolina-Chapel Hill and University of California-San Francisco, the Human Research Ethics Committee (Medical) at the University of the Witwatersrand in South Africa, and the Mpumalanga Department of Health and Social Development Research Committee.

### Community randomization

Communities were randomized at a 1:1 ratio, resulting in 11 intervention communities and 11 control communities. In order to achieve a balanced allocation of control and intervention communities with respect to covariates hypothesized to be associated with the primary outcome, gender norms, a restricted randomization scheme was employed [36]. First, all possible two-arm allocations were enumerated and examined to see how they balanced with respect to community characteristics from the 2011 AHDSS that might be associated with gender norms: community population size, average education, number of working residents in the community, number of foreign residents, proportion temporary migrants, and proportion female headed households. A reduced list of 50 allocations from the total 466,918 restricted allocations was randomly chosen and one was selected by a community representative during a community meeting. Community representatives and leaders from all of the communities agreed to participate in the study.

### Survey sampling

The sampling frame for the baseline and endline surveys was the 2011 and the 2013 Agincourt HDSS annual census, respectively, limited to households with 18–35 year old residents, and then stratified by gender to create ‘male’ and ‘female’ sampling frames. The target enrollment for each of the 22 communities (11 control and 11 intervention) was 55 individuals with 27–28 males and females per community. Only one individual per home was sampled for recruitment. Eligibility criteria for participation in the survey included: resides in the home (spends a majority of nights in a 7-day week within the home), is 18–35 years of age per confirmed date of birth, is the gender assigned to the home (i.e., male or female) and has lived in the study area for the past 12 months. Written informed consent was obtained from all participants in the survey and was offered in the local language, Shangaan, or English. The survey was interviewer-administered in Shangaan or English using Computer Assisted Self-Interview (CAPI) in which the interviewer directly entered responses into a tablet computer.

### Measures

Exposure is defined as the community randomization assignment. The primary endpoint for assessing intervention impact is gender norms, as measured by the Gender Equitable Men’s Scale (GEMS). This scale was originally developed in Brazil and has been adapted for use in the African context [37]. The scale used in the present study was based on an Ethiopian version with 24 items, which achieved high internal consistency reliability [38]. Wording of select items was changed in consultation with local research team members to increase appropriateness for the local context. A split-sample exploratory and confirmatory factor analysis was conducted using baseline data and resulted in unidimensional scales for men (17 items) and women (13 items), with higher scores representing more equitable gender norms. Items fell into four content areas: sexual relationships (e.g., “Men are always ready to have sex”); violence (“A woman should tolerate violence to keep her family together”); reproductive health and disease prevention (“It is a woman’s responsibility to avoid getting pregnant”); and household roles and decision-making (“A man should have the final word about decisions in his home”). Individuals’ scores were the sum of all items (each item ranged from 1–3).

Secondary endpoints for the study include having multiple (two or more) sexual partners in the last 12 months, sexual partner concurrency (two or more ongoing sexual partnerships within last three sexual partners), inconsistent condom use with last three partners, intimate partner violence (perpetration and experienced), and recent hazardous/harmful drinking. IPV victimization and perpetration was defined as reporting at least one of seven types of physical and sexual IPV on a World Health Organization questionnaire adapted for South Africa [39]. Hazardous/harmful drinking was defined as a score of 8 or above using the Alcohol Use Disorder Identification Test (AUDIT) [40]. Measures of community mobilization were also developed by the research team to monitor change processes in each of the 6 mobilization domains; the development and performance of these measures is reported elsewhere [41].

### Sample size

Power and sample size needed to detect changes in the primary endpoint of interest, the GEMS score, were determined for the male and female population. Assuming a sample of 600 subjects in each of the two arms, an intra-cluster correlation of 0.05 and an average cluster size of 55 resulted in an estimated design effect of 3.7, thus reducing the effective sample size to 162 for each arm. For men, with an effective sample size of 81 and estimated GEMS standard deviation of seven (score range of 17–51), the estimated power to detect a four-point increase in GEMS scores was 91 %. For women, with an effective sample size of 87 and an estimated standard deviation of six (score range of 13–39), the estimated power to detect a three-point increase was 80 %.

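### The two sex-specific effective sample sizes exceed the total per arm, and neither stated power (91% men, 80% women) follows from the printed inputs at a 5% level

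*Protocol article*

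**What the plan says.** The Sample size section starts from both sexes together: "Assuming a sample of 600 subjects in each of the two arms, an intra-cluster correlation of 0.05 and an average cluster size of 55". It reports that these inputs "resulted in an estimated design effect of 3.7, thus reducing the effective sample size to 162 for each arm".

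It then gives one power statement for each sex:

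- Men: "For men, with an effective sample size of 81 and estimated GEMS standard deviation of seven", a four-point difference, power 91%.
- Women: "For women, with an effective sample size of 87 and an estimated standard deviation of six"; "the estimated power to detect a three-point increase was" 80%.

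The section gives no significance level and does not say whether the test is one- or two-sided.

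The Survey sampling section sets the target for each community at "55 individuals with 27–28 males and females per community", with 11 communities in each arm. The Planned endline analysis section says that men and women will be analysed separately, so the two sex-specific powers are the ones that apply to the primary endpoint, the GEMS score.

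**The concern.** The paragraph prints every quantity needed to check it except alpha, and the quantities disagree in two separate ways.

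First, the effective sample is 162 per arm and the sexes are recruited equally, yet the effective numbers for men and women add up to more than 162. Second, the women's inputs look too favourable for a power of only 80%: half a standard deviation (3/6) with 87 effective subjects per arm should give clearly more.

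This paragraph is the article's only justification for the trial's size. A reader of a null result in women would take the chance of missing a three-point difference to be 20%, when the printed inputs imply about 9% to 11% at the conventional level. If the inputs are what was misprinted, the assumptions shown are not those that were used, and the reader cannot tell which.

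**Working it through.** **Inputs.** From Sample size: 600 per arm, ICC 0.05, cluster size 55; men n = 81, SD 7, difference 4, power 91%; women n = 87, SD 6, difference 3, power 80%. From Survey sampling: 27–28 of each sex per community, with 11 communities per arm. Assumed, because it is not stated: two-sided alpha 0.05.

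**Step 1: the figures that reproduce.**

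- Design effect = 1 + (55 − 1) × 0.05 = 3.7, as printed.
- Effective n per arm = 600/3.7 = 162.2, printed as 162.
- Half of 162 is 81, as printed for men.

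**Step 2: the women's 87.**

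- 81 + 87 = 168, against 162.
- At a design effect of 3.7, an effective 87 needs 87 × 3.7 = 322 women per arm. The recruitment target gives 11 × 27 = 297 to 11 × 28 = 308.
- This step does not involve alpha.

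**Step 3: power.** Power = Φ(d / (SD × √(2/n)) − 1.96), with n the effective number per arm.

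- Men: 4 / (7 × √(2/81)) = 3.64; Φ(3.64 − 1.96) = 95.3%. Stated: 91%.
- Women, n = 87: 3 / (6 × √(2/87)) = 3.30; Φ(3.30 − 1.96) = 91.0%. Stated: 80%.
- Women, n = 81: 3 / (6 × √(2/81)) = 3.18; Φ(3.18 − 1.96) = 88.9%.

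**Step 4: other readings of the same inputs.**

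| Reading | Men (stated 91%) | Women, n = 87 (stated 80%) |
|---|---|---|
| Two-sided 0.05, normal | 95.3% | 91.0% |
| Two-sided 0.05, t on 2n − 2 df | 95.1% | 90.6% |
| Two-sided 0.05, t on 20 df (22 communities − 2) | 93.3% | 88.0% |
| One-sided 0.05, normal | 97.7% | 95.1% |
| n read as the total of both arms | 73.0% | 64.5% |
| Two-sided 0.025, normal | 91.9% | 85.5% |
| Two-sided 0.02, normal | 90.5% | 83.4% |
| Two-sided 0.01, normal | 85.6% | 76.5% |

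**Step 5: could one unstated alpha give both figures?** The two-sided alphas at which computed power rounds to the printed value are:

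| Reference | Men, 91% | Women (n = 87), 80% |
|---|---|---|
| Normal | 0.0200–0.0236 | 0.0134–0.0148 |
| t on 2n − 2 df | 0.0217–0.0254 | 0.0145–0.0159 |
| t on 20 df | 0.0342–0.0389 | 0.0238–0.0258 |

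In no row do the two ranges overlap.

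**Step 6: what would yield the printed powers at two-sided 0.05.** Men would need n = 67 or SD 7.7. Women would need n = 63 or SD 7.06. Two coincidences are worth knowing: the women's printed inputs give 91%, the value printed for men, and the women's n and difference with the men's SD of 7 give 80.7%. Either may point to a transposed figure or a mixed-up SD, but neither can be confirmed from the article.

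**The case against.** The strongest reply is that alpha is not stated, that an article may leave it to the full protocol, and that the power mismatch is therefore conditional. Stricter levels do come close for one sex at a time. At two-sided 0.025, men have 91.4% with a t test on 160 df, and women have 80.1% with t on 20 df. If 87 is a slip for 81, a two-sided alpha of about 0.02 gives 90.5% and 80.4%, close to both printed values.

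Part of this stands. The exact size of the power error depends on the assumed level, and a stricter level cannot be excluded for either sex alone. But the two matches at 0.025 need a different reference distribution for each sex. The match at 0.02 concedes that 87 is wrong and relies on a level that the article nowhere mentions. Nothing here makes 81 + 87 equal 162.

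It is also fair to say that the printed powers err on the low side at 5%, that both surveys are dated in the past, and that no analysis or decision rule uses these percentages. That limits the consequences but does not make the paragraph correct. The suggested causes in Step 6 are possibilities, and the conclusion does not rest on them.

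**Conclusion.** The concern holds. The effective sample sizes are inconsistent whatever alpha was used: 168 against 162 per arm, or 322 women implied against 297–308 targeted.

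At two-sided 0.05 the men's power is understated by about 4 percentage points (95.3% against 91%) and the women's by about 11 (91.0% against 80%), or about 9 with the consistent n of 81 (88.9%). With the printed inputs, no single alpha reproduces both powers under any of the three reference distributions tried.

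The sizes rest on the assumed 5% level, equal allocation, and effective n read as a per-arm figure. They also keep the article's design effect of 3.7, which uses all 55 respondents per community. Whether that suits an analysis by sex, with 27–28 per community, is a separate question. The error does not show that the trial is underpowered on its own assumptions.

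**What to change.** Correct the Sample size paragraph:

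1. State the significance level and whether the test is one- or two-sided.
2. Replace the women's 87 with 81 if the 3.7 design effect and the equal split are kept, or explain where 87 comes from.
3. Confirm the women's SD. If it was 7 rather than 6, say so and recompute: with n = 81 and two-sided 0.05 the power would be 77.9%.
4. Restate both powers from the inputs shown. With SDs of 7 and 6, 81 per arm for each sex and two-sided 0.05, these are about 95% for men and 89% for women, or about 93% and 86% with a t reference on 20 df. State which reference is used.

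The cost is a text correction. Sample and conduct do not change.
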